**Fig. 3 Fig3:**
[figure not shown]
Susceptibility of the pyrethroid-resistant *Anopheles coluzzii* Akron strain to insecticides in study nets. Chlorfenapyr, pyriproxyfen and alpha-cypermethrin exposures were performed in WHO bottle bioassays while deltamethrin exposures were performed in WHO filter paper tube tests. Approximately 100 mosquitoes of each strain were exposed for 1 h to each insecticide in replicates of 25. For pyriproxyfen, mosquitoes were blood-fed before exposure and their ovaries dissected after 72 h to assess ovary development

Based on results from these preliminary bioassays, the testing plan in Table 2 will be used in laboratory bioassays for monitoring the bioefficacy of each active ingredient in the different ITN brands in the trial. In line with WHO guidelines, ITN bioefficacy at each timepoint will be expressed in terms of the proportion of ITNs passing the efficacy criteria for each active ingredient in cone bioassays or tunnel tests.

**Table 2 Tab2:** Summary of laboratory bioassay methodology and outcome measures for assessing the insecticidal durability of Interceptor^®^ G2 and Royal Guard^®^ in Benin compared to Interceptor^®^

ITN type	Brand name	Active ingredient	Mosquito strain	Mosquito age and status (N)	Primary test method (exposure time)	Key outcome measures	ITN efficacy criteria	Remarks/additional tests
Pyrethroid-only	Interceptor	alpha-cypermethrin	Susceptible *An. gambiae* s.s. Kisumu	unfed, 3–5 days old (40–50/net)	cone bioassays (3 min)	Knockdown, 24 h Mortality	knock-down ≥ 95% or mortality ≥ 80%	Tunnels for failed nets
Pyrethroid-chlorfenapyr	Interceptor G2^a^	alpha-cypermethrin	not tested	not tested	not tested	not tested	not tested	not tested due to lower dose of pyrethroid
		chlorfenapyr	Pyrethroid-resistant *An. coluzzii* Akron	unfed, 5–8 days old (100/net)	Tunnel tests (overnight)	72 h Mortality and Blood-feeding inhibition	Mortality ≥ 80% or Blood-feeding inhibition ≥ 80%	1 net piece per ITN
Pyrethroid- pyriproxyfen	Royal Guard	alpha-cypermethrin	Susceptible *An. gambiae* s.s. Kisumu	unfed, 5–8 days old (40–50/net)	cone bioassays (3 min)	Knockdown, Mortality	knock-down ≥ 95% or mortality ≥ 80%	Tunnels for failed nets
		pyriproxyfen	Pyrethroid-resistant *An. coluzzii* Akron	blood-fed, 5–8 days old (80–100/net)	cone bioassays (3 min) plus ovary dissection after 72 h	% reduction in fertility relative to control^b^	Reduction in fertility relative control	> 30% fertility required in control

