For bioefficacy of pyriproxyfen in Royal Guard^®^, blood-fed 5–8 days old mosquitoes of the pyrethroid-resistant *An coluzzii* Akron strain will be exposed for 3 min in cone bioassays and assessed for the impact on ovary development using dissection. Dissections will be performed under microscope by trained technicians, 72h after exposure. Mosquitoes presenting with Christopher stage V ovaries will be classified as fertile (Fig. 4) [31] and the proportional reduction in fertility relative to control unexposed mosquitoes at each bioassay will be determined for each ITN. A total of 80–100 blood-fed mosquitoes will be tested against each Royal Guard^®^ ITN in replicates of 5 mosquitoes per cone and 4 cones per ITN piece. As there are currently no WHO defined cut-offs for the reproductive effect of PPF-treated ITNs in bioassays, the pass rate of Royal Guard® nets at each timepoint will be assessed based on their capacity to reduce the fertility of exposed mosquitoes relative to the untreated control. Only tests for which at least 30% of unexposed mosquitoes are found fertile will be considered valid. Efficacy in these cone bioassays will be considered the final endpoints for performance of pyriproxyfen in Royal Guard^®^; no further tests will be performed in tunnels with failed nets.

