### Statistical analysis

Data from the surveys at 6, 12, 24, and 36 months will be used to calculate attrition, functional survival and median survival time using Kaplan–Meier estimators. For functional survival, nets reported as given away, sold, or stolen will be excluded from the analysis. Negative binomial regression will be used to compare hole surface area between the different ITN types. Data on WHO cone bioassays and tunnel tests will be obtained from 30 nets of each product type sampled at each time point. A chi-squared test will be used to assess the proportion of nets of each ITN type passing the WHO criteria for alphacypermethrin, chlorfenapyr and pyriproxyfen bioefficacy based on combined cone and tunnel tests. Proportional outcomes (mortality, blood-feeding, exophily) from the experimental hut trials will be compared at each time point using mixed effects logistic regression, with huts, sleepers, net replicate and nightly observational error included as random or fixed effects [33]. Numerical outcomes (hut entry) will be compared using negative binomial regression. A separate model will be fitted for each outcome to determine whether there is (i) a significant change over time, and (ii) a significant difference between ITNs washed 20 times and 36-month-old naturally aged ITNs. Analysis will be performed on STATA or the package *lme4* of the R software.

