Current WHO ITN evaluation guidelines define specific thresholds for determining the efficacy of ITNs in insecticidal durability bioassays. Nets that induce ≥ 95% knockdown and/or ≥ 80% mortality in cone bioassays or ≥ 80% mortality and/or ≥ 90% blood feeding inhibition in tunnel tests are considered efficacious. While proposing these same efficacy criteria for the laboratory bioassays for alpha-cypermethrin and chlorfenapyr bioefficacy in the study nets, it is recognized that these cut-offs were primarily developed for fast-acting pyrethroid insecticides on nets and may need to be modified for non-pyrethroid insecticides. Indeed, new draft WHO guidelines proposed for ITN prequalification aim more for a weight of evidence approach and do not allude to specific efficacy thresholds [39]. The weight of evidence approach may be suitable for assessing individual ITN products but could be challenging for comparing between ITN product brands and making programmatic and procurement decisions, which is usually the main objective for ITN durability studies. Efficacy criteria for the sterilizing effects of pyriproxyfen on ITNs are yet to be defined in WHO guidelines. Further studies investigating correlations between the sterilizing effects of Royal Guard^®^ nets in laboratory bioassays and their epidemiological performance against clinical malaria in the current trial, may contribute towards the identification of a suitable cut-off for the impact of pyriproxyfen in ITN durability studies.

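### The pyriproxyfen pass-rate test relies on a WHO criterion the protocol says does not exist, and the substitute rule has no threshold, so substantial partial loss of activity would be missed

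*Protocol article*

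**What the plan says.** The Statistical analysis section of the protocol article plans a chi-squared test whose outcome is the "proportion of nets of each ITN type passing the WHO criteria for alphacypermethrin, chlorfenapyr and pyriproxyfen bioefficacy". Cone and tunnel results are to be taken together for this. The text before Table 2 makes the proportion of nets passing, for each active ingredient, the way bioefficacy is expressed at every timepoint.

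For pyriproxyfen in Royal Guard, Laboratory bioassays and strain selection says: "As there are currently no WHO defined cut-offs for the reproductive effect of PPF-treated ITNs in bioassays". The Discussion agrees: "Efficacy criteria for the sterilizing effects of pyriproxyfen on ITNs are yet to be defined in WHO guidelines". In place of a cut-off, nets are to be judged "based on their capacity to reduce the fertility of exposed mosquitoes relative to the untreated control", and the efficacy-criteria cell of Table 2 reads "Reduction in fertility relative control". The same section makes the cone result final for pyriproxyfen, with no tunnel follow-up of failed nets. By contrast, the alpha-cypermethrin cell of that column is numeric: "knock-down ≥ 95% or mortality ≥ 80" (per cent). Table 2 also lists the percentage reduction in fertility as the key pyriproxyfen outcome.

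**The concern.** Two things do not fit. First, the analysis refers to a WHO criterion and to combined cone and tunnel results. For pyriproxyfen the protocol elsewhere says that the criterion does not exist and that tunnels will not be used. Second, the substitute rule states no minimum reduction, confidence limit or significance level. Taken at face value, any observed shortfall in fertility against the control is a pass.

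Durability of the non-pyrethroid ingredient is a central question for Royal Guard. A pass rate that starts at about 100%, and stays there while nets lose half their sterilizing effect, cannot describe the gradual decline that a three-year durability study is meant to measure.

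**Working it through.** **Inputs from the protocol article.** Five mosquitoes per cone and 4 cones per piece (Laboratory bioassays); 4 pieces per net after baseline and 5 at month 0 (Table 1); control fertility of at least 30% for a valid test; 30 nets per product per timepoint (Statistical analysis; Table 1 has 50 at month 36).

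**Reproducing the stated number.** 5 × 4 × 4 = 80 and 5 × 4 × 5 = 100, which matches the stated 80–100 mosquitoes per Royal Guard net.

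**Assumptions.** The article gives neither the number of control mosquitoes nor the true control fertility. I take 80 controls and control fertility p of 30–90%. All 80 exposed mosquitoes are assumed to be dissected.

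**Pass probability if any observed reduction passes.** Let X ~ Bin(80, p(1 − r)) be fertile exposed mosquitoes and Y ~ Bin(80, p) fertile controls, where r is the true reduction. The net passes if X < Y. Exact enumeration gives:

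| True reduction r | p = 30% | p = 50% | p = 70% | p = 90% |
|---|---|---|---|---|
| 0 (inert) | 46.6% | 46.9% | 46.6% | 44.7% |
| 20% | 77.9% | 88.4% | 96.1% | 99.8% |
| 30% | 88.9% | 96.8% | 99.6% | 100% |
| 50% | 98.7% | 99.9% | 100% | 100% |
| 98% | 100% | 100% | 100% | 100% |

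The 98% row uses the reduction reported for the bottle assay as a full-activity benchmark; it was not measured on a net.

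**Sensitivity.** With 100 v 100 mosquitoes an inert net passes 45.3–47.2%. With overdispersion (intra-cluster correlation 0.02–0.10) it passes 48–49%. If only 50 v 50 are dissected, a 30% reduction passes 82.2–99.9% and a 50% reduction 95.6–100%.

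**What the chi-squared test sees.** Suppose all 30 fully active nets pass and k of 30 aged nets fail. The Pearson statistic without continuity correction is 60k/(60 − k). For k = 3 it is 180/57 = 3.16; for k = 4 it is 240/56 = 4.29. The 5% critical value is 3.84, so at least 4 failures in 30 are needed. From Bin(30, 1 − pass probability), the chance of that is:
- all nets at a 50% reduction: below 0.1% at every p considered;
- all nets at a 30% reduction: about 43% at p = 30%, 1.5% at p = 50%, and below 0.01% at p = 70%;
- all nets inert: above 99.9%.

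**A significance-type rule instead.** With 80 v 80, requiring a one-sided 0.025 z-test passes 2.4–2.6% of inert nets. Requiring the 95% confidence interval for the fertility ratio to lie below 1 passes about 2.4%. Under the interval rule a net with a 50% reduction still passes 61%, 90% and 99.5% of the time at p = 30%, 50% and 70%.

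**The case against.** The strongest reply is that the pass proportion is not the only source of information on pyriproxyfen. The percentage reduction is to be determined for each net, with comparison against new unused nets. The hut trials at 12, 24 and 36 months record fertility of blood-fed survivors, and chemical content is measured at 0, 12, 24 and 36 months. That stands: the collected data could show a decline, and the weakness is confined to the pass-rate analysis. But the pass proportion is the declared bioefficacy summary, and the pass-rate test is the only laboratory bioassay analysis named in the Statistical analysis section.

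It can also be said that the text does not rule out a significance criterion, which a fuller document might state. That is fair, and the 45–47% figure depends on the literal reading. It does not remove the contradiction over the WHO criterion and the tunnel tests. Nor would such a rule cure the insensitivity, because most half-active nets still pass.

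A reader might infer that the chi-squared test pits Interceptor G2 (tunnel only, resistant strain, 72 h) against Interceptor (cone with tunnel follow-up, susceptible strain, 24 h), and so compares test systems rather than nets. The article does not state that contrast. It expresses results by active ingredient, and the differing assays are deliberate and justified. Only a clarification is warranted.

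**Conclusion.** The point holds in limited form. For pyriproxyfen, the analysis as written conflicts with two other places in the protocol on the existence of a WHO criterion, and with one on the use of tunnel tests. The rule offered instead has no threshold. Read literally, with 80 v 80 mosquitoes and control fertility of 30–90% (both assumed), it passes 45–47% of inert nets, 89–100% of nets with a 30% reduction and 98.7–100% of nets with a 50% reduction. The inert-net figure is insensitive to these assumptions; the figures for partial loss vary with control fertility.

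It would be tempting to conclude that loss of pyriproxyfen would be hidden altogether. The figures do not support that: total loss in all nets would take the pass rate from about 100% to about 47%, which 30 v 30 nets would almost certainly detect. What this test misses is substantial partial loss.

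**What to change.** In Statistical analysis, delete the reference to WHO criteria and to tunnel tests for pyriproxyfen. Make the fertility reduction already listed as the key outcome in Table 2 the main pyriproxyfen bioassay analysis: model fertile/dissected counts by mixed-effects logistic regression, with random effects for net and test day, against the concurrent unexposed control and new Royal Guard, by months of use.

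If a pass rate is kept, label it study-specific and secondary, and prespecify its rule and the control sample size. A rule that only asks the confidence interval to exclude 1 deals with inert nets but should not be the measure of decline.

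As a clarification, state that between-brand chi-squared tests are made within an active ingredient, that is, alpha-cypermethrin in Royal Guard v Interceptor.

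The cost is a change of analysis wording. The model uses counts and concurrent controls already planned. According to Status of study, bioassays on nets up to 24 months were still under way and follow-up surveys had been completed only to 24 months, so the change could precede the final analysis.

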Each hut trial will last 9 weeks and will involve 9 consenting human volunteers sleeping in huts from dusk to dawn 6 days of each week of the trial. Treatments will be rotated each week using a randomized Latin Square Design to control for bias due to hut position and to minimize carry over effects between treatments. Sleepers will be rotated daily to control sleeper attractiveness to mosquitoes. On the 7th day of each week, huts will be cleaned and aired in preparation for the next rotation cycle. The trials will run for a total of 54 nights and replicate nets collected from the field will be rotated between huts on successive nights (one net per night). Nets will be made available for laboratory bioassays and chemical analysis as described earlier, immediately after they have been tested in experimental huts.

The efficacy of each ITN hut treatment at each timepoint will be measured in terms of the following outcome measures:Percentage reduction in mosquito entry relative to the control (deterrence)Percentage of mosquitoes dead after 72 h,Percentage of mosquitoes exiting into the veranda trapPercentage reduction in mosquito blood-feeding relative to the control untreated netsPercentage reduction in proportion of fertile surviving blood-fed mosquitoes after dissection relative to surviving blood-fed mosquitoes in the untreated control hut

WHO susceptibility bioassays will be performed to assess the susceptibility of the wild vector population at the Cove experimental hut station to the insecticides in the study nets during each hut trial.

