### Experimental hut trials to compare 36 months old naturally aged field nets to washed nets

To investigate the capacity of ITN washing (20 times) to predict the performance of field aged ITNs, we will conduct another hut trial comparing nets of each ITN type washed 20 times to 36 months naturally aged field nets. ITN washing will follow WHO protocols for hut trials [13]. A total of 78 replicate 36 months old naturally aged field-collected nets of each ITN type will be tested over 78 nights. Six replicates of unwashed and washed nets of each ITN type will be tested, and each net will be given six 4 × 4cm holes following WHO guidelines. The hut trial will also be performed at the Côvè experimental hut station and will consist of the following 13 hut treatments.Untreated net—6 replicatesInterceptor^®^ (new unused)—6 replicatesPermaNet^®^ 3.0 (new unused)—6 replicatesRoyal Guard^®^ Benin (new unused)—6 replicatesInterceptor^®^ G2 (new unused)—6 replicatesInterceptor^®^ (washed 20 times)—6 replicatesPermaNet^®^ 3.0 (washed 20 times)—6 replicatesRoyal Guard^®^ Benin (washed 20 times)—6 replicatesInterceptor^®^ G2 (washed 20 times)—6 replicatesInterceptor^®^ (36-months field net)—78 replicatesPermaNet^®^ 3.0 (36-months field net)—78 replicatesRoyal Guard^®^ (36-months field net)—78 replicatesInterceptor^®^ G2 (36-months field net)—78 replicates

The trial will run for 13 weeks and will involve 13 consenting human volunteers sleeping in huts from dusk to dawn 6 days of each week of the trial. As with the other hut trials, treatments will be rotated each week using a randomized Latin Square Design and sleepers rotated daily and huts cleaned and aired on the 7th day of each week in preparation for the next rotation cycle. The trial will run for a total of 78 nights and the replicate 36 months old naturally aged field nets will be rotated between huts on successive nights (one net per night). Efficacy will be measured in terms of mosquito deterrence, mortality (72h), exiting, blood-feeding inhibition, reduction in fertility of blood-fed survivors as described earlier.

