Despite the methodological modifications we propose for laboratory bioassays in this study, it is unclear whether typical ITN laboratory bioassay techniques (cone bioassays and tunnel tests) would be sufficiently informative of the insecticidal durability of dual AI ITNs as these methods were developed for pyrethroid-only ITNs [22, 23]. Other bioassay methods under consideration for dual AI ITNs are the WHO wire ball assay [13, 40] and the net-in-tube test [22] that provide a more forced contact between the mosquito and the net potentially resulting in greater levels of AI pick up from the net than in cone bioassays. Given the mode of action of chlorfenapyr described earlier, these assays would be less suitable for the assessment of its activity in Interceptor^®^ G2 as they provide less opportunity for mosquito movement and host seeking. In addition, our preliminary studies assessing the baseline activity of pyriproxyfen in Royal Guard^®^ using the net-in-tube method resulted in higher levels of mosquito mortality with high intensity pyrethroid-resistant strains leaving very few blood-fed survivors for ovarian dissection. These methods due to the forced contact they provide may therefore be less suitable for monitoring changes in the bioefficacy of the pyriproxyfen component in Royal Guard^®^ over time. Experimental hut trials are more representative of real-life settings and are widely used for evaluating ITNs under semi-field conditions for product development and for decision-making about their deployment [41]. In these trials, ITNs are tested overnight against wild free-flying vector mosquitoes entering naturally into the huts in the presence of a human volunteer and the levels of blood-feeding inhibition and mortality rates achieved are used as proxies for their capacity to provide personal and community protection to users. Hence the assessment of field collected ITNs in experimental hut trials proposed in this study will provide additional insights into the impact of these dual AI ITNs against malaria as they age under operational conditions.

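### Hut blood-feeding is compared only among mosquitoes that enter; a cheap added model of blood-fed mosquitoes per hut-night would test the quantity behind personal protection

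*Protocol article*

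**What the plan says.** The protocol article lists five hut outcomes under Experimental hut trials to assess insecticidal durability. The first is "Percentage reduction in mosquito entry relative to the control (deterrence", so the article itself treats entry as something the net changes. Killing is given as "Percentage of mosquitoes dead after 72 h". Blood-feeding is given as a percentage reduction against the untreated net, without saying whether counts or proportions are meant. For the trial of washed against 36-month nets the list is "mosquito deterrence, mortality (72h), exiting, blood-feeding inhibition, reduction in fertility of blood-fed survivors as described earlier".

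The Statistical analysis section settles how these are tested: "Proportional outcomes (mortality, blood-feeding, exophily) from the experimental hut trials will be compared at each time point using mixed effects logistic regression". For counts it says "Numerical outcomes (hut entry) will be compared using negative binomial regression", and it adds "A separate model will be fitted for each outcome". It names no model for the number of blood-fed mosquitoes.

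On use, the Discussion says of hut trials that "the levels of blood-feeding inhibition and mortality rates achieved are used as proxies for their capacity to provide personal and community protection to users". The Background likewise values huts because they show more realistically how far an ageing net protects the householder and the community.

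**The concern.** The denominator of the blood-feeding proportion is the mosquitoes found in the hut, and that number is itself affected by the net. The comparison is therefore conditional on a post-treatment quantity. It answers how well a net stops feeding by mosquitoes that have come in. For the sleeper, what counts is how many mosquitoes feed in a night: the number entering multiplied by the proportion that feed.

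The two agree when nets deter equally and can disagree when they do not. The contrasts open to this are those between products, and those between new, washed and field-aged nets. At stake is any statement on personal protection drawn from the blood-feeding test. The validity of that test among entrants is not in question.

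**Working it through.** No figure in the plan can be reproduced on this point. The only hut power figure, an 80% target, concerns killing and is to be checked by simulation after the first round. The check is therefore algebra plus assumed rates.

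**Condition for disagreement.** Let N be the number entering the control hut, d the deterrence and p the proportion fed among entrants.

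- Blood-fed mosquitoes with a net = N × (1 − d) × p.
- Suppose net A has the higher proportion fed (pA > pB), so the planned test favours B.
- A still gives fewer blood-fed mosquitoes when (1 − dA)/(1 − dB) < pB/pA, that is, when the entry ratio A/B is below the ratio of proportions fed B/A.

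**Thresholds for the entry ratio A/B (assumed feeding rates).**

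- 30% v 25% fed: 25/30 = 0.833, so A must cut entry by more than 16.7% relative to B.
- 25% v 20%, or 30% v 24%: 0.80.
- 30% v 20%: 0.67.
- 40% v 20%: 0.50.

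**Example 1 (assumed).** A: 40% deterrence, 30% fed. B: no deterrence, 25% fed.

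- Blood-fed per 100 control entries: A = 100 × 0.60 × 0.30 = 18; B = 100 × 1.00 × 0.25 = 25.
- Ratio 18/25 = 0.72, so A gives 28% fewer.
- Odds ratio for feeding, B v A = (0.25/0.75)/(0.30/0.70) = 0.78, favouring B.

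**Example 2 (assumed).** Control 60% fed. A: 50% deterrence, 30% fed. B: 10% deterrence, 20% fed.

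- Blood-feeding inhibition: A = 1 − 30/60 = 50.0%; B = 1 − 20/60 = 66.7%. B ranks first.
- Blood-fed per 100 control entries: control 60; A = 100 × 0.50 × 0.30 = 15; B = 100 × 0.90 × 0.20 = 18.
- Personal protection: A = 1 − 15/60 = 75%; B = 1 − 18/60 = 70%. A ranks first.
- Entry ratio 0.50/0.90 = 0.56, below the 0.67 threshold.

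**Simulation at the size of the annual trials.** It used 54 nights per net, 600 runs, overdispersed entry, night-to-night variation in feeding (SD 0.5 on the logit scale), two-sided 0.05, and 5, 10 or 20 control entries per night (assumed). Quasi-binomial and quasi-Poisson models stood in for the planned mixed logistic model and for a negative binomial count model.

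- Example 2: the proportion model found A significantly worse in 75%, 95% and 99% of runs. That is correct among entrants, although A truly gives fewer blood-fed mosquitoes. The point estimates of the two analyses had opposite directions in 74%, 82% and 86%.
- In the same runs the count model found A significantly better in only 12%, 15% and 21%. The true difference (15 v 18) is small and counts are noisy.
- Deterrence 65% v 10%, same feeding rates: both analyses were significant in opposite directions in 21%, 61% and 78%.
- Deterrence 20% v 10%, entry ratio 0.80/0.90 = 0.89, above the threshold: A gives 24 and B 18, so both measures favour B.
- Equal deterrence (20% each): point estimates disagreed in 5%, 4% and 2% of runs, and never with both significant.

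The disagreement therefore comes from differential entry and fades when entry is similar.

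**The case against.** Much of the case for the plan stands. Deterrence is a listed outcome with its own model, so a reader cannot fairly say that entry is ignored. What is missing is a test or interval for the combination; multiplying two separately fitted estimates gives a point value only. The proportion among entrants is also a sound estimand for insecticidal durability, which is the heading under which these trials are planned.

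The Discussion sentence describes hut trials in general and is not an analysis instruction. No objective or hut outcome is called personal protection. A reader might infer that the plan's ranking of nets on personal protection is reversed. The documents do not support that: they set no such ranking and give no rates for these nets in huts.

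A reader might also infer that killing should be tested as a count. Arithmetic can reverse that order too: 50% v 10% deterrence with 70% v 50% mortality gives 35 v 45 killed per 100 control entries. But a dead-mosquito count mixes insecticidal activity with deterrence, marks a net down for keeping mosquitoes out, and does not measure the sleeper's protection. Mortality among entrants is the right killing outcome to keep.

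It can be said that a fuller protocol or analysis plan may hold a blood-fed count, and that the outcome list leaves count or proportion open. The Statistical analysis section nonetheless places blood-feeding among the proportional outcomes. If the outcome list does mean counts, that section has no matching test. The transmission model may combine entry and feeding, but its method is only cited, and it is not a hut comparison between nets.

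**Conclusion.** The point holds for blood-feeding alone, as a cheap improvement. No test named in the article addresses blood-fed mosquitoes per hut-night, although the article values hut trials partly for what they say about personal protection. The proportional analysis is correct for entrants. It can order nets differently from the blood-fed count when the entry ratio falls below the ratio of proportions fed, for example when net A cuts entry by more than 16.7% relative to B at 30% v 25% fed.

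Every deterrence and feeding rate used here is an assumption. The documents supply none, so disagreement is shown to be possible, and its likelihood is unknown. With similar deterrence the planned analysis orders the nets correctly on both measures.

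**What to change.** In the Statistical analysis section, add for each hut contrast, including washed against 36-month nets, a negative binomial model of the number of blood-fed mosquitoes per hut-night. Give it the same hut, sleeper, net and night terms as the proportional models. State that any conclusion on personal protection rests on this model. Keep the logistic models for blood-feeding inhibition, mortality and exophily, the separate model for entry, and mortality among entrants as the killing outcome.

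The cost is one more outcome to fit and report per trial, with noisier estimates than the proportion. Data collection does not change: entry and feeding are already recorded, and negative binomial regression is already planned for entry.
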